### Study type and design

This study will be a randomized controlled, crossover, 3-arm, clinical trial. The protocol description followed the SPIRIT [40] and the TIDieR [41] guidelines (Fig 1 and S1–S3 Tables). Participants will undergo a health history questionnaire, anthropometric measures which include height, body mass, waist circumference and body composition, a period of familiarization and strength assessment. At least 4 days after the strength tests, they will carry out 3 randomized experimental sessions, separated by at least 4 (but no more than 28) washout days, as it has been shown that the acute effect of exercise on improved insulin action lasts up to 2 days [42]. In case the sessions are scheduled 21 to 28 days apart, participants will be required to perform a familiarization session 2 weeks after the preceding (and 1 to 2 weeks before the following) experimental session to avoid defamiliarization. The interval between experimental sessions will be recorded and reported in the final manuscript, and discussed accordingly. To avoid the variation in insulin sensitivity across the menstrual cycle [43–49], in case premenopausal women are included in the sample, they will be assessed in the follicular phase (days 1–14) [9, 26, 50–52] of their menstrual cycle. Two of the experimental sessions will be performed with strength exercises: a high-volume session [3 sets per exercise–high volume]; a low-volume session [1 set per exercise–low volume]; and a control session: no exercise. In the exercise sessions, 7 exercises will be performed for the major muscle groups (1 –hex bar squat; 2 –bench press; 3 –leg press; 4 –lat pulldown; 5 –leg extension; 6 –shoulder press; 7 –leg curl; Fig 2), totaling 21 sets in the high-volume session and 7 sets in the low volume session [24]. The sessions will be held at night, between 8:00 pm and 9:00 pm. This time schedule for the sessions is ecologically valid, as exercise in the evening is commonly observed in fitness centers due to time constraints for exercising earlier during the day [13, 53], and it has been shown that night-time exercise does not affect sleep duration or quality [53]. The next morning between 7:00 am and 8:00 am (between 10 and 11 hours after the session), an OGTT will be performed in a local clinical laboratory. Participants will respond to scales of feeling, enjoyment, and self-efficacy after the exercise sessions. All sessions will be supervised by a certified fitness professional. The experimental design is illustrated in Fig 3.

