### Statistics

#### Sample size

The sample size was calculated from the literature [10, 12, 16, 17, 19, 23, 26, 27, 77] using the G*Power program (Heinrich-Heine-Universität Düsseldorf, Germany, version 3.1.9.6), inserting the parameters for a one-way ANOVA, effect size of 0.6 probability of error type alpha of 0.05 and power (probability of error type 1 –beta) of 0.9. With these parameters, 14 individuals will be needed (actual power of 0.93). Due to the usual sample loss of 25–40%, we will initially recruit 20 participants. In order to promote participant retention, frequent text messages will be sent as reminders to follow the instructions, and to show up in the scheduled sessions. Also, in case the participant misses a session, all effort will be made to reschedule as long as it is within 28 days of the previous session. Dropout reason will be recorded and reported in the manuscript.

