Data will be expressed as the mean and standard deviation with a confidence interval of 95%. For the analysis of data normality, we will perform the Shapiro-Wilk test. For normally distributed data, analysis of variance will be used with one source of variation (experimental situation). If a significant main effect was observed, post hoc Tukey test was used. For non-parametric data, the Kruskal-Wallis test was used, or Friedman’s test, when necessary. Effect size was calculated and interpreted as follows: <0.2 = no effect, 0.2–0.49 = low effect, 0.5–0.79 = medium effect, and greater than 0.8 = large effect [81, 82]. The significance level will be 5%. The Prisma program (GraphPad Software, San Diego, CA-USA–version 8.4.0) will be used to analyze the results. The trial will be reported following the CONSORT guidelines [83, 84].

As stated above under **Blinding procedures**, the researcher responsible for data analysis (the statistician) will be blinded for group allocation. For that, a collaborator outside the research team will double enter data coded for allocation into a computer in separate spreadsheets so that the researcher responsible for data analysis can assess data without having access to information about the allocation. Allocation will only be revealed after statistics are run. In case there are doubts about data entry (missing values, or values outside the reference range), the researcher responsible for data analysis will contact the collaborator outside the research team responsible for double entry of the data to check accuracy. There will be no interim analysis.

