#### Weaknesses

This study cannot be completed in a double-blind manner, as the participants and the researchers who will be present during the sessions will be aware of the treatment (high- or low-volume or control session). However, the professionals at the clinical lab who will collect and analyze the blood will be blinded to treatment, as well as the researcher who will perform the statistics. We will include obese men and women over 40 years old, so our results might not be readily translated to other clinical populations, such as younger, healthy individuals or individuals living with DM2. Furthermore, individuals with potentially different levels of insulin resistance might be included in this study, and greater exercise-induced improvement in insulin resistance has been observed in individuals with higher levels of baseline insulin resistance [26, 92]. Thus, this factor can also increase results variability. However, it should be pointed out that studying overweight/obese subjects regardless of their insulin resistance levels or fasting glucose impairment status is commonplace in the related literature [8, 93–95]. Nevertheless, the fact that participants will be their own control minimizes this potential source of variability. Moreover, individual results will be presented and discussed accordingly should individual levels of insulin resistance affect average group results. Furthermore, DM2 patients will be excluded, following our exclusion criteria. Also important to point out, participants might not follow the dietary and physical activity instructions the day before and the day of the sessions, which might also be confounding factors when interpreting our results. However, we will stress the importance of following these instructions by sending frequent text messages, and adherence will be verified when they report to the gym, and we will ask them to report what they ate to the nutritionist, which we believe increases adherence to diet prescription. Finally, per our study design, we will assess two significantly different strength exercise volumes, and by default time commitment, as lack of time is usually listed as one of the main reasons not to adhere to exercise [30]. Thus, our study design is not intended to explore a potential dose-response relationship between strength exercise volume and improvements in insulin sensitivity, although this approach would bear practical implications.

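### The three-session crossover is given tests that are not stated as within-participant: an ANOVA with session as its only source of variation, and Kruskal-Wallis or Friedman with no rule for choosing

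*Protocol article*

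**What the plan says.** The design is not in doubt. Study type and design states: "This study will be a randomized controlled, crossover, 3-arm, clinical trial". The Weaknesses section answers the worry about mixed levels of insulin resistance by saying that "the fact that participants will be their own control minimizes this potential source of variability".

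The Data analysis section then names the tests:

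- For normally distributed data, "analysis of variance will be used with one source of variation (experimental situation".
- For the follow-up comparisons, "If a significant main effect was observed, post hoc Tukey test was used".
- For the rest, "For non-parametric data, the Kruskal-Wallis test was used"; the same sentence goes on to offer Friedman's test if it is needed.

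No participant term, paired form or repeated-measures form is mentioned, and nothing says when Friedman becomes necessary.

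The Sample size section uses the same model, "inserting the parameters for a one-way ANOVA, effect size of 0.6 probability of error type alpha of 0.05", with "power (probability of error type 1 –beta) of 0.9". It arrives at 14 individuals and an actual power of 0.93. No within-participant correlation is given.

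**The concern.** Three values from one person are correlated. An ANOVA whose only source of variation is the session puts the differences between people into the error term, and those are the differences that the crossover is meant to remove. Kruskal-Wallis does the same on ranks: it assumes independent samples, and no outcome compared across these sessions has them. The stated analysis therefore does not deliver the own-control benefit claimed under Weaknesses.

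The question of practical interest, set out in the Discussion, is whether low-volume exercise improves insulin action. The pairwise comparison with control answers that. If its standard error is too large, a real low-volume effect may be missed, or low and high volume may look alike merely because the interval is wide.

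**Working it through.** **Inputs from the protocol article.** Three conditions, 14 participants, effect size 0.6, alpha 0.05, target power 0.90, stated power 0.93. The 0.6 is read as Cohen's f, the ANOVA effect size. That reading reproduces the stated figures.

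**Assumptions.** The documents give no within-participant correlation (rho), so a range is shown. Equal correlation between all pairs of sessions is assumed throughout. Equally spaced means (control, low, high) are assumed in the simulations.

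**1. Reproducing the sample size.**
- Independent-groups one-way ANOVA, 14 observations per session: lambda = N f² = 42 × 0.36 = 15.12, df 2 and 39, power 0.928. This matches 0.93.
- The smallest independent-groups N with power of at least 0.90 is 39 (13 per session), power 0.906.
- Repeated-measures ANOVA: lambda = n m f² / (1 − rho), df 2 and 26. With n = 14, m = 3, rho = 0, lambda is again 15.12 and power is 0.917; 14 is then the smallest n that reaches 0.90. With rho = 0.05, power is 0.930. With rho = 0.5, lambda = 30.24, power is 0.998, and 8 participants would give 0.924.

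The stated pair (14 and 0.93) therefore fits unpaired data or a correlation of about zero. Either way, pairing earns essentially no credit.

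**2. Standard error of a between-session difference.** Write s² for the variance of one value.
- Unpaired: √(2s²/n). Paired: √(2s²(1 − rho)/n). Ratio: 1/√(1 − rho).
- rho 0.5: 1/√0.5 = 1.41. rho 0.7: 1/√0.3 = 1.83. rho 0.8: 1/√0.2 = 2.24.

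**3. True size of the unpaired ANOVA at nominal 5%** (simulated, n = 14): 0.3% to 0.5% across runs at rho 0.5, 0.1% or less at rho 0.7, and about 0% at rho 0.8. Kruskal-Wallis behaves alike (0.3% at rho 0.5, about 0% at 0.8). The within-participant tests stay at about 5%.

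**4. Power at the planned effect.** With equal spacing, the step between neighbouring conditions is f × √1.5 = 0.6 × 1.225 = 0.735 SD, so the extremes lie 1.47 SD apart. The Tukey comparison is made only after a significant F. Simulation error is about 0.01.

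| rho | Overall F: unpaired / within-participant | Low volume vs control, Tukey: unpaired / within-participant |
|---|---|---|
| 0.5 | 0.97 / 1.00 | 0.28 / 0.61 |
| 0.7 | 0.98 / 1.00 | 0.25 / 0.85 |
| 0.8 | 0.99 / 1.00 | 0.23 / 0.96 |

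**5. Power of the overall test at smaller effects.**
- f about 0.245 (0.6 SD between extremes: step 0.3 SD, and 0.3 / 1.225 = 0.245): unpaired 0.16 against 0.46 at rho 0.5, and 0.08 against 0.86 at rho 0.8.
- f = 0.3, Kruskal-Wallis against Friedman: 0.28 against 0.50 at rho 0.5, and 0.20 against 0.88 at rho 0.8.

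**The case against.** The strongest reply is that a one-factor repeated-measures ANOVA also has a single factor of interest. The own-control remark and the naming of Friedman suggest that the authors may have had that in mind. This reading is possible, but it is nowhere stated, and the section that names the tests should settle it. The sample-size figures lean towards the unpaired form without proving it, since a repeated-measures calculation with almost no correlation gives nearly the same result.

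Four stronger readings are tempting, and the documents do not support them:

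- *The plan uses only independent-groups tests.* It does not: Friedman stands in the same sentence as Kruskal-Wallis. The fault there is two non-equivalent tests with no rule for choosing.
- *Most of the design's power is thrown away.* At the planned f = 0.6 this is untrue of the overall test. It holds for smaller effects, and for the low-volume comparison once the correlation is about 0.5 or more. The documents do not give that correlation.
- *The results would be invalid in the sense of false positives.* With positive correlation the error runs the other way. Per-session means and SDs are also unaffected; only standard errors, intervals and tests for between-session differences are wrong.
- *The missing period term is itself an error.* Session order is randomised, and such a term is commonly left to an analysis plan. The protocol also has its own provisions for incomplete data, so a mixed model is one acceptable remedy and not the only one.

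**Conclusion.** The point stands in limited form. The named tests do not fit the crossover as written, and they conflict with the protocol's own-control argument. The standard errors of between-session differences and the size of the tests would be wrong, in the conservative direction, for any positive within-participant correlation.

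How much this matters depends on a correlation that must be assumed. At the planned effect the overall test is nearly untouched. The low-volume versus control comparison loses more than half its power at a correlation of 0.5 or above, given equal spacing of the conditions. Because that comparison carries the practical message, and the cure is a matter of wording, it should be corrected before analysis.

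**What to change.** Reword the analysis paragraph under Data analysis so that only one analysis is possible:

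- State that the ANOVA and the Tukey comparisons are within-participant. A repeated-measures ANOVA would do. So would a mixed model with condition, period and a random participant intercept, which also uses participants who complete one or two sessions.
- Report 95% confidence intervals for the paired between-session differences.
- Delete Kruskal-Wallis and keep Friedman as the only rank alternative.

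It would also help to state in the Sample size section which form of ANOVA was used and what correlation was assumed.

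The cost is a rewritten paragraph and, if a period term is included, software that fits it. No further data or participants are needed.

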## Discussion

### Potential impact and significance of the study

An acute bout of strength exercise has been shown to improve insulin action and glucose metabolism [23]. However, current guidelines for the prescription of strength exercise suggest that 8 to 30 sets could be performed [25], which means a ~4-fold difference in exercise volume and thus time commitment. Furthermore, high-volume strength exercise might discourage individuals with low self-efficacy, which might diminish long-term adherence to a training program. Therefore, assessing the effects of low- vs high-volume strength exercise on insulin action and glucose metabolism bears clinical relevance because if low-volume strength exercise elicits improvement in these parameters, individuals might be more motivated and feel more confident in performing low-volume strength exercise.

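### The bands read 'no effect' from a point estimate below 0.2, but with 14 participants that estimate cannot rule out a medium effect on the protocol's own scale

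*Protocol article*

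**What the plan says.** The Data analysis section of the protocol article sets out the bands as "Effect size was calculated and interpreted as follows: <0.2 = no effect", then 0.2 to 0.49 as low, then "0.5–0.79 = medium effect, and greater than 0.8 = large effect". It does not say which effect size is meant, which SD standardises it, or whether the bands apply to the signed or the absolute value. The 95% CI mentioned at the start of the same paragraph belongs to the mean and SD used to describe the data, not to the effect size.

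The bands stand beside a testing route at the 5% level: one-factor analysis of variance, or a rank-based test where needed. For the pairwise step the text reads "If a significant main effect was observed, post hoc Tukey test was used".

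On numbers, the Sample size section says "14 individuals will be needed (actual power of 0.93" and, for attrition, "Due to the usual sample loss of 25–40%, we will initially recruit 20 participants".

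**The concern.** 'No effect' is a conclusion of absence. It needs an interval narrow enough to exclude effects that matter, and the rule asks for none.

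The wording matters most when the overall test is not significant. The Tukey comparisons are then not made, and the bands are the only pairwise reading that the section describes. The pairwise questions are the practical ones. The Discussion rests the trial's value on the possibility that "if low-volume strength exercise elicits improvement in these parameters, individuals might be more motivated". A report that low volume has no effect against control, or that high and low volume do not differ, could rest on an estimate that is also compatible with a medium difference. In the other direction, a low or medium label can be taken as a finding when it is noise.

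**Working it through.** **Inputs.** Bands at 0.2, 0.5 and 0.8 (Data analysis). Three conditions in a crossover, so contrasts are within person (Study type and design). n = 14, with 20 recruited (Sample size). The within-person correlation ρ is not given; the values below are assumptions. Data are taken as normal.

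**The plan's own figure.** The inputs are "one-way ANOVA, effect size of 0.6 probability of error type alpha of 0.05". Reading 0.6 as Cohen's f, λ = 0.6² × 42 = 15.12. With 2 and 39 df (14 independent people per condition) power is 0.928, which matches the stated 0.93. As repeated measures with ρ = 0 and 2 and 26 df it is 0.917. So 14 is the right n for this check.

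**1. What a 'no effect' label leaves open: paired d (mean difference ÷ SD of differences).** The 95% CI comes from the noncentral t distribution with 13 df.
- d = 0: limits ±1.96/√14 = ±0.52.
- d = 0.19: -0.34 to 0.72.

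The interval closest to excluding 0.5 in both directions is the one at d = 0, and it still reaches 0.52. So no paired d with absolute value below 0.2 excludes a medium effect in both directions. The stated 25–40% loss from 20 leaves 15 to 12 people. At d = 0 the limits are then ±1.96/√15 = ±0.51 and ±1.96/√12 = ±0.57, so the result does not depend on exactly 14. Only if all 20 complete does d = 0 exclude 0.5 (±1.96/√20 = ±0.44).

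**2. The same for d scaled by the raw SD.** The approximate half-width is t(0.975; 13) × √(2(1−ρ)/14), with t = 2.160.

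| ρ (assumed) | Half-width | Upper limit at d = 0.19 |
|---|---|---|
| 0.5 | 0.58 | 0.77 |
| 0.7 | 0.45 | 0.64 |
| 0.8 | 0.37 | 0.55 (0.555) |
| 0.9 | 0.26 | 0.45 |

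For d just under 0.2 (0.199) to exclude 0.5, the half-width must be below 0.301. That requires ρ > 1 − 7 × (0.301/2.160)² = 0.86. For d = 0 it requires ρ > 1 − 7 × (0.5/2.160)² ≈ 0.63.

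**3. How often a null contrast earns a label of low or larger.**
- Paired d: 2 × P(t₁₃ > 0.2√14 = 0.748) = 0.47, whatever ρ is.
- d treated as independent (ρ = 0): 2 × P(t₂₆ > 0.2√7 = 0.529) = 0.60.
- Raw-SD d, simulated: 0.46, 0.35, 0.25 and 0.12 at ρ = 0.5, 0.7, 0.8 and 0.9.
- Omnibus f: P(F₂,₂₆ > 0.04 × 26/2 = 0.52) = 0.60, or 0.47 with 39 error df.
- Partial eta-squared: about 0.05 with 26 error df, 0.01 with 39.
- If all 20 complete, paired d gives 0.38.

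For comparison, a paired d must reach 2.160/√14 = 0.577 for an unadjusted p < 0.05. The whole low band and the lower part of the medium band therefore lie below significance for a paired contrast.

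**The case against.** The strongest reply is that the bands are descriptive. The section sets a 5% testing route, and nothing in it says that a label replaces a test or decides the trial's conclusion. A non-significant overall test is itself a reading, and means, SDs and 95% CIs are to be reported. This stands. A reader might infer that the plan declares an effect in about half or more of null outcomes; the text does not support that, because a low label is not a claim of significance. It does not rescue 'no effect', which states absence whatever test stands beside it.

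The reply is also right that the chance-label rate has no single value. It depends on an effect size and a correlation that the article does not give: about 12% to 60% for d and f, and about 5% or less if partial eta-squared were meant. Leaving the exact definition to a fuller plan would be ordinary for an article. The fault is in the rule that is stated.

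A reader might also note that, taken literally, a value below 0.2 includes every negative one, so that a fall in HOMA-IR would count as no effect. That cannot be added to the 47%, which uses absolute values; on the signed reading the null rate for paired d is 23%. Stating 'absolute value' settles the matter.

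Finally, the power of the ANOVA-then-Tukey route is a separate question and is no evidence against the bands.

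**Conclusion.** The point holds in a limited form. Labelling an effect size below 0.2 as no effect reads absence from a point estimate that cannot show it. For paired d with 14 people, and across the 12 to 15 left by the protocol's own loss range, such a label never excludes a medium effect. For raw-SD d just under 0.2, it does so only if the within-person correlation exceeds about 0.86. A low or larger label arises by chance in about 47% of null paired contrasts, so the bands grade magnitude and carry no evidence of an effect in either direction.

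This rests on normal data, on reading the bands as absolute values of a standardised difference (or of f where stated), and on assumed correlations. It does not show that the planned tests have an inflated error rate, nor that the labels are meant as the trial's conclusion.

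**What to change.** In the Data analysis section:

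- Name the effect size and its standardiser, and apply the bands to its absolute value.
- Replace 'no effect' with 'trivial', and say that the words describe magnitude only.
- For high versus control, low versus control and high versus low, report the within-person mean difference and its standardised value with multiplicity-adjusted 95% CIs (for example Tukey simultaneous intervals), whatever the overall test shows.
- Base any claim of an effect on the planned tests or the adjusted intervals. Claim absence or similarity only if the interval lies wholly within a margin stated in advance. Call everything else inconclusive.

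The adjustment is needed: if an effect were claimed whenever any one of three unadjusted paired intervals excluded 0, simulation at n = 14 with no true effect gives at least one such claim in about 12.6% of outcomes.

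The cost is a change of wording and a few more intervals, with no new data. More comparisons will be reported as inconclusive. With an unadjusted interval already about ±0.52 wide at d = 0, similarity within ±0.2 could almost never be claimed at this sample size, so any margin has to be chosen and justified with that in view.
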